## Abstract

**Background:**

Over the past ten years MRSA has become endemic in hospitals and is associated with increased healthcare costs. Critically ill patients are most at risk, in part because of the number of invasive therapies that they require in the intensive care unit (ICU). Washing with 5% tea tree oil (TTO) has been shown to be effective in removing MRSA on the skin. However, to date, no trials have evaluated the potential of TTO body wash to prevent MRSA colonization or infection. In addition, detecting MRSA by usual culture methods is slow. A faster method using a PCR assay has been developed in the laboratory, but requires evaluation in a large number of patients.

**Methods/Design:**

This study protocol describes the design of a multicentre, phase II/III prospective open-label randomized controlled clinical trial to evaluate whether a concentration of 5% TTO is effective in preventing MRSA colonization in comparison with a standard body wash (Johnsons Baby Softwash) in the ICU. In addition we will evaluate the cost-effectiveness of TTO body wash and assess the effectiveness of the PCR assay in detecting MRSA in critically ill patients. On admission to intensive care, swabs from the nose and groin will be taken to screen for MRSA as per current practice. Patients will be randomly assigned to be washed with the standard body wash or TTO body wash. On discharge from the unit, swabs will be taken again to identify whether there is a difference in MRSA colonization between the two groups.

**Discussion:**

If TTO body wash is found to be effective, widespread implementation of such a simple colonization prevention tool has the potential to impact on patient outcomes, healthcare resource use and patient confidence both nationally and internationally.

**Trial Registration:**

[ISRCTN65190967]

## Background

Over the past ten years there has been a dramatic increase in the number of infections caused by MRSA in several countries, including the United Kingdom (UK) [1]; this pathogen is now endemic in hospitals throughout the country. It appears that although many patients begin by being colonized, without any clinically evident infection, between 30% and 60% of colonized critically ill patients subsequently develop an infection syndrome attributable to the organism [2,3]. In fact, colonization pressure (number of MRSA carrier patient-days/total patient-days) is a major independent predictor of MRSA infection in a given critically ill population [4].

MRSA infection appears to be associated with greater attributable mortality than infection with methicillin-sensitive Staphylococcus aureus (MSSA), based on a recent meta-analysis of bacteraemia outcomes [5], although this may reflect the vulnerability of the patient population infected by MRSA, rather than greater virulence of the organism *per se*. Nevertheless, compared to MSSA, infections with MRSA demand treatment with antimicrobial agents of greater toxicity and acquisition costs; many of these drugs also require frequent monitoring of serum levels, further adding to the total cost of therapy [1,5]. Moreover, MRSA infection is associated with prolonged length of hospital stay, including duration of Intensive Care Unit (ICU) stay; using data from the National Audit Office, nosocomial infection is estimated to be associated with, on average, 11 additional days in hospital and total costs of 2.8 times that of uninfected patients [6-10]. Indeed, even without progression to infection, colonized patients require increased healthcare resource in the numerous measures implemented to limit the spread of MRSA to other patients. Investigators in Canada, using a cost model, estimated the additional cost per patient episode arising from MRSA colonization (without infection) equivalent to £650 [11]. Applying these costs to local ICU surveillance data, new MRSA colonization alone may add around £65,000 per annum to cost of care in a 17-bed ICU, aside from costs of prolonged ICU stay.

MRSA acquisition among critically ill patients represents a particular problem. Although it is difficult to compare data from different institutions and different countries because of inconsistencies in surveillance approaches, ICUs typically emerge with the highest incidence of MRSA compared to other wards [12]. Furthermore, ICUs may have a pivotal role in the dissemination of MRSA within an institution [13]. Moreover, prolongation of ICU stay attributed to MRSA infection has particular resource implications, arising from the exceptional cost of care in this setting [7]. Therefore, reducing the burden of MRSA in an ICU has potential to exert tangible benefits both within that ICU and in other clinical departments. Clearly, an intervention which might reduce the prevalence of MRSA has the potential to exert an extremely favourable impact on both patient outcomes and hospitalization costs.

Reducing the prevalence of MRSA among hospitalized patients requires several, complex, interrelated interventions. Fundamentally, such a strategy requires prompt identification of colonized individuals and robust methods to reduce transmission to noncolonized patients. In this study, we propose to address both of these requirements. First, in the form of a randomized clinical trial we aim to evaluate the impact of daily washing with a 5% tea tree (Melaleuca alternifolia) oil preparation on new MRSA acquisition among ICU patients. Second, in the form of a prospective observational study we aim to verify in this setting a rapid molecular assay for the detection of MRSA, with reference to extant culture-based methods.

Tea tree oil (TTO) is a naturally occurring chemical with broad microbicidal activity which is known to include MRSA [14,15]. Only a small number of clinical trials have been conducted using preparations containing TTO. These establish proof of concept that topical formulations suitable for human use may eradicate MRSA skin colonization [16-18]. In a randomized controlled trial (RCT) of TTO (4% nasal ointment and 5% body wash) compared to routine care (nasal mupirocin and triclosan body wash) for MRSA decolonization, 5 of 15 patients in the TTO group compared with 2 of 15 in the routine care group were successfully decolonized, although this difference was nonsignificant due to small sample size [17]. In the second published RCT for MRSA decolonization 224 patients were enrolled and received either standard treatment (nasal mupirocin and chlorhexidine body wash) or TTO (10% nasal cream and 5% body wash) [16]. Overall, 41% receiving TTO were successfully decolonized, similar to standard care. On subanalysis, TTO was superior for decolonization of superficial skin sites.

The utility of TTO preparations for MRSA decolonization has not been further evaluated in robust clinical trials. Furthermore, in spite of the laboratory and clinical evidence supporting the efficacy of such preparations in eradicating MRSA, there are no published data evaluating the role of TTO in the prevention of MRSA acquisition. Since TTO has proven efficacy, low toxicity and, as it is not part of the standard therapeutic armoury, prophylactic use does not expose a current MRSA treatment to the threat of resistance, we propose that this would be a logical strategy to investigate. In view of the resource implications of MRSA colonization and infection, it is imperative that interventions which focus on reducing these are also subjected to cost-effectiveness analyses.

With reference to identifying colonized patients more promptly, we propose to verify an established in-house MRSA PCR assay. This is an area of immense need since the current standard of culture-based diagnosis, with a turnaround time of 48–96 hours (depending on the result) is suboptimal. Therefore, noncolonized patients may be at risk of MRSA acquisition arising from exposure to colonized (but still unidentified) patients for an unacceptably long period of time. We have optimized a real-time PCR-based assay in our laboratory which has the potential to facilitate a same-day turnaround for MRSA detection. The assay, however, needs to be verified using a large number of clinical specimens from a large number of patients, with reference to the current diagnostic standard, before it is acceptable to introduce this new test to routine care.

## Methods

### Research hypotheses

The primary research hypothesis is that MRSA colonization among critically ill patients will be reduced by daily washing with 5% TTO body wash in comparison with a standard body wash (Johnsons Baby Softwash). The secondary hypotheses are that 5% TTO body wash is more cost-effective than a standard body wash (Johnsons Baby Softwash); and that there is no difference in sensitivity and specificity between a PCR-based assay for detection of colonization with MRSA and the standard culture method.

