### Data collection methods and assessments: TTO evaluation and PCR verification

Data will be collected in a standardized manner across both sites according to Standard Operating Procedures. In both sites, patients will have screening specimens for MRSA carriage (using conventional culture methods on nasal and groin samples) carried out as a component of routine care by the nurse responsible for their care on admission to the ICU. For pragmatic reasons, duplicate specimens for processing by the PCR assay will only be taken in the RICU in the Belfast HSCT. All specimens will be obtained prior to either intervention commencing and will consist of swabs from both the nose and groin of all patients. Patients whose admission screening is positive by either method will be removed from the study (see exclusion criteria).

To facilitate verification of the PCR assay in the Belfast HSCT study population, its results will be compared to the culture results. Where there is disagreement between the culture and PCR results both will be repeated. In instances when the culture is persistently positive but the PCR assay persistently negative, this will be recorded as a false-negative PCR result (assuming a true-positive culture result). In instances when the culture result is persistently negative but the PCR assay is persistently positive, this will be recorded as a true-positive PCR result (assuming a false-negative culture result). If either test is not consistently positive or negative, it will be recorded as equivocal.

The presence of established major risk-factors for MRSA will be recorded, so that each can be analyzed as a covariate. These are:

• Total number of antibiotic-days during the ICU episode [24-26].

• Age (blocked by 10-year intervals).

• Number of comorbidities

• Intravascular catheter-days (number of devices × number of days) [27,28].

• Length of ICU stay [28,29].

• Severity of illness on admission to ICU [29].

Several other MRSA risk factors exist, such as transfer from high prevalence clinical units, multiple prior hospitalizations and residence in a nursing home. However, if participants are culture-negative at the time of admission to ICU, then these factors are not significant and therefore will not be recorded.

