#### Hypothesis 3: Verification of PCR assay

Agreement between MRSA screening results obtained by the PCR assay versus conventional culture with reference to the definitions of true and false positivity above will be evaluated, to estimate the sensitivity, specificity, positive and negative predictive values of the PCR assay in this population.

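### The PCR hypothesis claims no difference from culture, but its assigned analysis estimates PCR accuracy only, and the specificity half is met by construction

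*Protocol article*

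**What the plan says.** Protocol article, Research hypotheses: one of the two secondary hypotheses is that "there is no difference in sensitivity and specificity between a PCR-based assay for detection of colonization with MRSA and the standard culture method". No margin or minimum accuracy is attached.

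Protocol article, Hypothesis 3: Verification of PCR assay: the analysis takes "Agreement between MRSA screening results obtained by the PCR assay versus conventional culture", applies the study's definitions of true and false positivity, and uses this "to estimate the sensitivity, specificity, positive and negative predictive values of the PCR assay in this population". Outcome measures lists the endpoint only as agreement between the two methods.

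Protocol article, Data collection methods and assessments: both tests are repeated where they disagree.

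- Persistently culture-positive and PCR-negative: "this will be recorded as a false-negative PCR result (assuming a true-positive culture result)".
- Persistently culture-negative and PCR-positive: "this will be recorded as a true-positive PCR result (assuming a false-negative culture result)".
- Otherwise: "If either test is not consistently positive or negative, it will be recorded as equivocal".

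The Background says the assay must be verified in many specimens and patients "before it is acceptable to introduce this new test to routine care". The same data collection section says that "duplicate specimens for processing by the PCR assay will only be taken in the RICU in the Belfast HSCT", and Table 1 schedules the PCR swabs at baseline only.

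**The concern.** The hypothesis concerns a contrast between two tests, while the analysis assigned to it describes one of them. Carried out as written, the analysis yields PCR sensitivity, specificity and predictive values, and nothing in it says whether the hypothesis is supported.

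The hypothesis is also framed unhelpfully. Its content is a null, so without a margin no result counts clearly as support. Nor is equality with culture the same as adequacy: two tests can be equally sensitive and both miss many carriers. The decision at stake is whether to bring the assay into routine care, and that turns on whether its accuracy is high enough.

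The discordance rules raise a further problem. They treat every persistent positive, by either test, as a true positive, which empties the specificity comparison of content.

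**Working it through.** **1. The plan's own figure.** The only sample size is for colonization: 13% in controls and a 40% relative reduction, so 0.13 × 0.6 = 7.8%; two-sided 0.05, 80% power. With p̄ = 0.104,

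n = [1.960 × √(2 × 0.104 × 0.896) + 0.842 × √(0.13 × 0.87 + 0.078 × 0.922)]² / 0.052² = 540 per group, or 1080 in total.

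The stated figure reproduces, but it does not size the PCR question.

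**2. Hypothesis against analysis.**

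| Needed for the stated hypothesis | In the Hypothesis 3 analysis |
|---|---|
| Sensitivity and specificity of PCR | Yes |
| Sensitivity and specificity of culture | No |
| Paired difference | Not named |
| Margin or minimum value | No |

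**3. What the discordance rules imply.** Ignore equivocal results. Let a = both positive, b = culture only, c = PCR only, d = both negative. Every patient in a, b or c is reference-positive; only d is reference-negative. Then:

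- PCR sensitivity = (a + c)/(a + b + c)
- culture sensitivity = (a + b)/(a + b + c)
- difference, PCR minus culture = (c − b)/(a + b + c)
- specificity of either test = d/d = 100%

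The specificity difference is therefore zero whatever the data show. The sensitivity difference is zero whenever b = c, however large both are.

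**4. Equal is not adequate (invented counts).** Take a = 20, b = 10, c = 10. Both sensitivities are 30/40 = 75% and the difference is 0. Against culture alone, PCR finds 20 of 30 (67%) and misses 10 (33%).

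**5. Precision.** The number of carriers found at admission in the Belfast unit is not given. Under assumed counts, exact (Clopper-Pearson) 95% intervals for PCR sensitivity are:

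| Detected / carriers | Estimate | 95% interval |
|---|---|---|
| 16/20 | 80% | 56% to 94% |
| 40/50 | 80% | 66% to 90% |
| 36/40 | 90% | 76.3% to 97.2% |

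**6. If a non-significant test were read as no difference.** The protocol plans no such test; this only illustrates the risk in the wording. Assume that 5% of detected carriers are PCR-only and 15% culture-only, a true 10-point deficit for PCR. The power of an exact McNemar test at 0.05 is:

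| Detected carriers (assumed) | Power |
|---|---|
| 20 | 3.2% |
| 40 | 17.2% |
| 60 | 30.8% |

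**7. If a margin were set.** For non-inferiority on the paired sensitivity difference (true difference 0, one-sided 0.025, 80% power), the reference-positive patients needed are approximately discordance × (1.960 + 0.842)² / margin²:

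| Margin | Discordance 5% | 10% | 20% |
|---|---|---|---|
| 10 points | 40 | 79 | 157 |
| 5 points | 157 | 314 | 628 |

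**The case against.** The strongest reply is that Hypothesis 3 is an estimation exercise. The 0.05 significance rule stands under Hypothesis 1, and no test is assigned to the PCR comparison. The reported PCR sensitivity would expose a poor assay: in step 4 it would read 75%. Agreement on duplicate specimens is already a paired comparison, and culture sensitivity and the paired difference can be derived from the same table. Interval methods, agreement statistics and a margin may sit in a full protocol or SAP that is not shown. This part is also a secondary, observational component and leaves the randomised comparison untouched.

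Most of this stands, and it limits the point. A reader might infer that the plan will declare the tests equivalent from a non-significant P value, and so report no difference in 69% to 97% of studies under the step 6 inputs. The documents do not support that: no such test is planned, and the carrier counts and discordance rates are assumptions. A reader might also infer that an assay missing many carriers would pass unseen. It would not, because its sensitivity would be reported.

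What the reply does not remove is the mismatch. The article states one hypothesis and assigns to it an analysis of a different quantity, and an SAP that inherits this wording inherits the problem. Nor does it answer the specificity point, which follows from rules that the article itself states.

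**Conclusion.** The point holds as a mismatch between a stated hypothesis and its analysis. The Hypothesis 3 analysis does not address the no-difference claim, and that claim, without a margin, would not show that PCR is accurate enough for routine use. The specificity half cannot fail, apart from equivocal results; this follows from the discordance rules and needs no assumption.

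The practical size depends on the number of carriers found, which the article does not give. If it is in the tens, the intervals in step 5 are wide enough that the assay's adequacy could remain open. The change should be made, but it concerns a secondary aim and does not bear on the primary result.

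**What to change.** **Research hypotheses.** Replace the no-difference statement with one of two:

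- an aim to estimate PCR accuracy, judged by whether the lower 95% confidence limit exceeds a minimum value that the sponsor fixes in advance; or
- non-inferiority of PCR to culture on the paired sensitivity difference, with a pre-set margin.

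**Hypothesis 3 analysis.** Report exact 95% intervals. If the comparison with culture is kept, report the paired difference with its 95% interval, and do not read non-significance as equivalence.

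**Reference standard.** Asking only for accuracy against culture would conflict with the discordance rules, which count persistent PCR-only positives as true. So report PCR sensitivity and specificity against the initial culture result, before discrepant results are resolved, alongside the composite reference. Draw no conclusion about specificity from the composite.

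**Cost.** A few sentences in Research hypotheses and Hypothesis 3, plus a matching statement of the reference standard where the discordance rules stand. No new data are needed, provided that the initial results are kept as well as the repeats. The downside is that the conclusion may become 'not yet shown' if few carriers are found.

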### Design and setting

This multicentre phase II/III prospective, open-label, randomized controlled clinical trial tests the effect of 5% TTO body wash versus standard body wash for prevention of MRSA colonization in critically ill adults. The study is being undertaken in two ICUs in two Health and Social Care Trusts (HSCT) in Northern Ireland. The Regional Intensive Care Unit (RICU) at the Belfast HSCT is a 17-bed intensive care unit (ICU) which receives general medical and surgical patients as well as patients both from regional specialty departments of the Royal Hospitals and from district general hospitals requiring level 3 care. The ICU at the South Eastern HSCT at the Ulster Hospital site is a 10-bed critical care unit which receives general medical and surgical patients requiring level 2 and level 3 care.

### Participants and sample size

All patients admitted to the ICUs during the study period will be eligible for inclusion in the study except those patients who fulfil the following exclusion criteria: less than 18 years of age; known to be colonized with MRSA at the time of admission; on admission, are judged as unlikely to remain in the ICU for at least 48 hours; are recruited, but whose pre-intervention MRSA screening tests are subsequently found to be positive (by standard culture); consent declined; and have a known sensitivity to TTO.

The primary outcome measure is the difference in MRSA colonization between groups at ICU discharge. The incidence of MRSA colonization during ICU admission in the study population is 13% (data obtained from the feasibility study conducted in one of the ICUs). A sample size of 1080 subjects (540 in each group) will have 80% power at a two-tailed significance level of 0.05 to detect a clinically significant difference of at least 40% in efficacy between 5% TTO and standard body wash. As the study will be confined to ICU, with nursing staff administering the study treatment, compliance will be guaranteed. Given the intensive monitoring in ICU, we do not expect any loss to follow-up.

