### Recruitment of patients, randomisation and consent

When a patient is admitted, the investigator will contact the on-line randomization centre in the Clinical Research Support Centre [a centre providing design, management and coordination services for clinical trials and other studies conducted within the Health and Personal Social Services in Northern Ireland and funded by the Research and Development Office, Northern Ireland]. The investigator will complete the screening form on-line and this will generate a screening number indicating whether the patient is randomized or excluded. The randomization centre will provide the investigator with the allocation to receive either intervention A or B. The investigator will then obtain the appropriate intervention for the patient, which will be stored on the ICU. A record of all patients not randomized, including the reason for not being recruited, will be maintained by the investigator.

As patients are at risk from immediate exposure to MRSA from admission to the ICU, the success of this study will be dependent on randomizing patients as soon as possible. Furthermore as patients will be critically ill, they will not have the capacity to be able to give or withhold informed consent. Delay in recruiting patients would mean a significant proportion of patients would be excluded. Therefore, as the intervention is low risk, we plan to randomize patients on admission and obtain prospective/retrospective consent from their legal representative as soon as possible. In addition, retrospective consent will be obtained from the patient as soon as they are competent. This approach has previously been adopted in trials in the critical care setting [19-21]. In line with The Medicines for Human Use (Clinical Trials) Regulations 2004 and to comply with the Research Governance Framework, consenting processes will be standardised, and reinforced via training prior to study start-up. The planned flow of patients through the study is illustrated in Figure 1.

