### Withdrawal from the study and the intervention

Individual patients will remain in the study until one of the following study termination criteria is reached: death; pre-intervention MRSA screening test is subsequently found to be positive; unit discharge; or patient or legal representative decline consent or request withdrawal from the study. The intervention will be continued in participating patients until one of the following intervention termination criteria is reached: adverse effect arising from either preparation; discharge from the unit; or MRSA colonization.

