### Statistical analyses

#### Hypothesis 1: TTO evaluation

For continuously distributed outcomes, differences between groups will be tested using independent samples t-tests, analysis of variance (ANOVA) and analysis of covariance (ANCOVA) with transformations of variables to normality if appropriate, or non-parametric equivalents. Chi-square tests (or Fisher's Exact tests) will be used for categorical variables. Major risk-factors for MRSA will be analyzed as covariates. Efficacy of intervention will be analysed on an intention to treat basis. A P value of ≤ 0.05 will be considered significant. A single final analysis is planned at the end of the trial.

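### The 1,080 carries no allowance for the removals planned after randomisation: the text must say what 1,080 counts and name the analysis set those removals leave

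*Protocol article*

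**What the plan says.** In the Protocol article, 'Participants and sample size' states: "A sample size of 1080 subjects (540 in each group) will have 80% power at a two-tailed significance level of 0.05", with the aim "to detect a clinically significant difference of at least 40% in efficacy between 5% TTO and standard body wash". The background incidence of colonisation is 13%, from a feasibility study in one of the units. No inflation is applied, and the reason given is: "Given the intensive monitoring in ICU, we do not expect any loss to follow-up".

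'Recruitment of patients, randomisation and consent' puts randomisation first: "we plan to randomize patients on admission and obtain prospective/retrospective consent from their legal representative as soon as possible". The Background gives 48–96 hours for a culture result, so the admission screen is read after allocation.

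Three sections then take randomised patients out:

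- 'Participants and sample size' lists among its exclusions recruited patients whose pre-intervention culture turns out positive, and declined consent.
- 'Withdrawal from the study and the intervention' ends participation for, among other reasons, "pre-intervention MRSA screening test is subsequently found to be positive; unit discharge; or patient or legal representative decline consent", or a request to withdraw.
- 'Data collection methods and assessments' removes patients whose admission screen is positive by either culture or PCR. PCR specimens are taken at the Belfast site only.

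The analysis section for Hypothesis 1 says: "Efficacy of intervention will be analysed on an intention to treat basis". It does not say how removed patients are handled.

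**The concern.** The sample size treats every subject as contributing an outcome, while the same document schedules two kinds of departure after randomisation. Close monitoring in intensive care helps to secure an outcome for patients who stay in the study. It does not stop a culture taken on admission from turning positive, or a relative from refusing consent.

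Two things are at stake. The first is the power claim: with no margin in the 540, any removal from a fixed 1,080 randomised takes power below the stated value. The second is the comparison itself. Allocation is open-label and consent may be sought once it is known, so refusal can depend on arm. An analysis that omits those patients is not intention to treat in the usual sense, and the label hides the one route by which selection could enter.

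**Working it through.** **Inputs from 'Participants and sample size'.** Control rate 13%; difference 40%; two-sided α 0.05; power 80%; 540 per arm. The text does not call the 40% relative, but that reading reproduces the stated number: 0.13 × (1 − 0.40) = 0.078, an absolute difference of 0.052. The mean rate is (0.13 + 0.078)/2 = 0.104.

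**Step 1: reproduce the plan's figure.** Pooled-variance formula, no continuity correction:

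n = [1.96 × √(2 × 0.104 × 0.896) + 0.8416 × √(0.13 × 0.87 + 0.078 × 0.922)]² / 0.052²

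= [1.96 × 0.4317 + 0.8416 × 0.4301]² / 0.002704 = 539.8 per arm.

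Rounded up, this is 540 per arm and 1,080 in total, with power 80.0% at 540. The stated figure is reproduced exactly, so the arithmetic is sound and the allowance for removals is zero.

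**Step 2: power if 1,080 is the number randomised.** The documents give no removal rate, so the share d is an assumption shown as a range, taken equally from both arms. With n = 540 × (1 − d):

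power = Φ{[0.052 × √n − 1.96 × 0.4317] / 0.4301}

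The detectable reduction comes from solving the Step 1 formula for the treated rate at 80% power with that n. The last column is 1,080/(1 − d), rounded up.

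| Assumed share removed | Remaining per arm | Power for 13% vs 7.8% | Relative reduction detectable at 80% power | Randomised to keep 1,080 |
|---|---|---|---|---|
| 0% | 540 | 80.0% | 40% | 1,080 |
| 5% | 513 | 78.0% | 41% | 1,137 |
| 10% | 486 | 75.7% | 42% | 1,200 |
| 15% | 459 | 73.3% | 43% | 1,271 |
| 20% | 432 | 70.7% | 44% | 1,350 |

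Example at 10%: (0.052 × √486 − 0.8461)/0.4301 = (1.1464 − 0.8461)/0.4301 = 0.698, and Φ(0.698) = 75.7%.

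**Step 3: power if 1,080 is the number retained.** Each arm then has 540 analysable patients and power is 80.0% as stated. What is missing is the statement that recruitment continues until that number is reached.

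**Step 4: the removals against the intention-to-treat label.**

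- *Positive admission screen.* The swab is taken before either wash begins, so the wash cannot affect the result. If the rule is applied alike in both arms, excluding these patients carries little bias. The set is then a modified intention-to-treat set and only needs to be called one.
- *Consent declined or withdrawn.* This can happen after allocation is known, so it can differ by arm. Omitting these patients can bias the comparison.
- *Which test removes a patient.* The exclusion list says standard culture; the data-collection section says either method. Because PCR runs at one site only, the two rules give different analysis sets, and the difference falls at that site alone.
- *Death.* End-of-study swabs are planned at death as well as at discharge, so death is not a planned loss of outcome and is not counted in d.

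**The case against.** The strongest reply is that 1,080 may already mean patients who survive the exclusions. The late-positive screen and declined consent are listed as exclusion criteria in the paragraph just before the sample size, so 1,080 subjects can be read as 1,080 not excluded, with recruitment continuing until they are accrued. Power is then 80%. This reply stands as a possible reading, and it makes the shortfall conditional. It does not settle the matter, because nothing in the article says which number is meant or whether removed patients are replaced.

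A second reply is that loss to follow-up normally means an enrolled patient whose outcome is not ascertained, and that excluding an ineligible carrier is something else. That is fair for carriers. It does not cover withdrawal of consent, and the sentence is the only justification offered for having no allowance.

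A third reply is that definitions of analysis sets, tables of removals and sensitivity analyses are often left to the analysis plan. That is right as far as their absence goes. The point here is narrower: rules that the article does state do not fit the label it states.

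A reader might also infer that power fails even under strict intention to treat, because carriers at baseline would count as events and dilute the effect. The documents do not support this. The primary outcome is new colonisation, which a patient positive before the intervention cannot have, and the plan removes such patients. Nor do the documents support saying that removals will go unreported: the article does not say so, and its flow diagram is not available here.

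**Conclusion.** The point holds in conditional form, at moderate severity. It is certain that 1,080 contains no allowance, that the plan removes patients after randomisation, and that the no-loss sentence and the bare intention-to-treat label do not accommodate this.

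It is not established that the trial is underpowered. That needs 1,080 to be the number randomised and a removal rate that is more than trivial, and the documents give neither. If both apply, the cost is about 2 percentage points of power at 5% removed, about 4 at 10% and about 9 at 20%. These figures assume equal removal from both arms and an unchanged 13% control rate.

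On bias, only consent refusal after a known allocation is a real route, and its size cannot be judged from the documents. It would be wrong to extend the charge to the removal of admission carriers.

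**What to change.** 1. State that 1,080 is the number of patients analysed, with recruitment continuing until it is reached; or restate the power or the detectable reduction for the number expected to remain, giving the assumed removal rate.
2. Replace the no-loss sentence with one that acknowledges the planned removals for positive admission screens and for declined or withdrawn consent.
3. Reconcile the exclusion list (culture only) with the data-collection section (either method, PCR at one site). Then name the primary set as modified intention to treat: all randomised patients with a negative pre-intervention screen and no refusal of data use, analysed as allocated.
4. Report removals by arm and reason, and add one sensitivity analysis for consent refusals, for example with their outcomes imputed at opposite extremes in the two arms.

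The cost is a few sentences and one extra analysis. If 1,080 is kept as the number randomised, the power claim becomes slightly less favourable. If it is the number analysed, more patients must be randomised, between about 1,137 and 1,350 for assumed removals of 5% to 20%.
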